### Neurological classification

The neurological evaluation is performed according to the International Standards for Neurological Classification of Spinal Cord Injury (ISNCSCI), a revision of ASIA classification [23,24]. Within the ISNCSCI-regime the ASIA impairment scale (AIS) as a measure for completeness of the injury, and the single neurological level of the lesion are assessed.

### Blood sample handling

Peripheral blood is collected under sterile conditions from each participant at each visit. All samples are labeled with a six-digit pseudonym and any personal information of the participants is removed. Overall, one 2 ml and one 6 ml Ethylenediaminetetraacetic acid (EDTA) BD Vacutainer®, two 3 ml Heparin BD Vacutainer® and one 8.5 ml Serum BD Vacutainer® are needed. Furthermore one 5 ml Cyto-Chex® blood collection tube (BCT) and two 2.5 ml PAXgene™ RNA tubes are collected (Figure 4). Blood samples for flow cytometric analysis are analyzed as soon as possible, preferably within 24 hours latest within 48 hours. Preservation of intracellular and extracellular surface markers is ensured by using Cyto-Chex® BCT [25,26].

**Figure 4 F4:**
[figure not shown]
**SCI-IDS Immunephenotyping – qualitative and quantitative measures.** Legend: Scheme of blood collection, sample preparation and analysis procedures. ConA = Concanavalin A, ELISA = Enzyme Linked Immunosorbent Assay, ELISPOT = Enzyme Linked Immunosorbent Spot, FACS = Fluorescence-activated cell sorting, IFN-g = Interferon-gamma, TNF-g = Tumor necrosis factor – gamma.

Supernatants from whole blood stimulation and further blood samples for secondary outcome measures are stored at -80°C for subsequent batch analysis (Figure 4). In the trial centers at Berlin and Zurich, one additional 8 ml BD Vacutainer® CPT™/Ficoll™ tube is collected for immediate preparation of Peripheral Blood Mononuclear Cells (PBMCs) for storage in liquid nitrogen. The handling of samples follows identical standard operating procedures and checklists at all trial centers.

### Immune profiling of SCI-IDS

The following investigations are performed to determine the immune status: i) immunophenotyping with lymphocyte subpopulations (B, T, NK cells), T cell subpopulation (CD3, CD4, CD8) and monocytic HLA-DR expression; ii) ex vivo T lymphocyte cytokine secretion such as ConA-induced IFN-g, TNF-α, IL-2, IL-4, IL-5, IL-10 secretion and staphylococcal enterotoxin B (SEB)-induced IL-17 production; iii) gene expression analysis for immune activation/deactivation related genes (mRNA expression); iv) circulating immune modulators: such as IL-6, epinephrine; v) indirect infection parameters: procalcitonin, C-reactive protein (CRP), LBP (lipopolysaccharide-binding protein).

Immunophenotyping using fluorescence-activated cell sorting (FACS) including quantitative measurement of monocytic HLA-DR expression as the primary outcome measure will be conducted according to standardized operation procedures established at the Institute of Medical Immunology (Charité - Universitätsmedizin Berlin, Germany) for clinical diagnostics of an immune suppression state [14]. HLA-DR belongs to the MHC class II molecules that are responsible for antigen presentation to CD4+ T-cells. Monocytic HLA-DR expression reflects the state of the adoptive immune competence as it is positively regulated by Th1 cytokines and negatively regulated by anti-inflammatory cytokines, stress hormones and some exogenous agents. Furthermore, monocytic HLA-DR expression is associated with the ability to produce pro-inflammatory mediators upon challenge by bacterial products such as lipopolysaccharides (LPS). Reduced monocytic HLA-DR expression has been established to correlate with an increased risk for infections in critically ill patients previously [14,27,28].

### Quantitative measures of HLA-DR expression

In contrast to the pilot study that measured HLA-DR expression on different cell types [6], the SCIentinel study measures quantitatively the amount of HLA-DR molecules per monocyte (in estimated numbers per cell). The reliability of the method has been previously approved in an inter-laboratory study [14].

The principle of the test is as follows. A mixture of Phycoerythrin (PE) beads conjugated with defined amounts of PE molecules is measured at the same instrument settings as the cells incubated with a mix consisting of anti-human HLA-DR-PE, anti-human CD14-PerCP-Cy5.5, and an inhibitor of HLA-DR turnover (BD Quantibrite™ HLA-DR/Monocyte reagent, BD Biosciences). The PE beads facilitate conversion of the FL2 axis into PE molecules bound per cell. The known ratio of PE to anti-HLA-DR antibody is used to convert the PE molecules per cell into antibodies per cell (AB/c). The anti-HLA-DR antibody, clone L243, reacts with a non-polymorphic HLA-DR epitope and is conjugated with PE molecules in a ratio of 1:1. The anti-CD14 antibody, clone MοP9, is conjugated with PerCP-Cy5.5. CD14 is expressed by the majority of monocytes. In addition, since the cyan dye component of PerCP-Cy5.5 binds to CD64, the anti-CD14 PerCP-Cy5.5 antibody detects all monocytes (CD14 brightly positive and weakly positive). The immunodiagnostical thresholds delineating a graded SCI-IDS penetrance are defined as indicated in Table 3 and were developed based on previous clinical trials after CNS injury [27].

**Table 3 T3:** Thresholds for the interpretation of the analysis of HLA-DR expression on monocytes

**Antibodies/cell**	**Interpretation**
> 15 000	Normal diagnostic findings
10 000 – 15 000	Immunodepression
5 000–10 000	Borderline immunoparalysis
< 5 000	Immunoparalysis

### Data management

Data are collected on a paper CRF (pCRF) basis. All patient’s data are managed with a six-digit pseudonym. At the coordinating center personnel familiar with the trial protocol check the filled pCRFs for completeness and consistency. Implausible or missing data may be corrected or added after consulting the investigator at the trial site through the study management (Queries). The corrected documents will be archived together with the completed CRFs. Data are entered and stored electronically in a database (Access) and are independently double-checked for correctness. The database has secured and restricted access centralized at IT-Center of Charité-Universitätsmedizin Berlin, Germany. Data backups are performed on a daily basis.

### Interim evaluation of recruitment status

An administrative interim evaluation for control of the estimated recruitment schedule after enrolment and follow up of approximately 50% of the calculated sample size has been performed. Patients recruited until April 2013 and followed up to July 2013 were included. The groups for comparison were analyzed for their concordance with the estimated sample size (Table 4). Furthermore the completeness of data for the main laboratory outcome parameters (flow cytometry) at each time point was assessed within the 'per protocol’ population (Table 5).

**Table 4 T4:** Administrative interim analysis of the recruitment status for patients without high-dose methylprednisolone treatment

**Groups**	**Overall n (%)**	**SCI T4 and above n (%)**	**SCI T5 and below n (%)**	**Control group n (%)**	**Drop out n**
**Estimated sample size**	118 (100)	48 (100)	31 (100)	39 (100)	n.a.
**Enrolled partients**	60 (51)	28 (58)	11 (35)	17 (44)	4

**Legend:** Sixty patients without high-dose methylprednisolone treatment were included into the SCIentinel trial from August 2011 to April 2013. The number of patients recruited into the group of SCI patients of the neurological level T5 or below was slightly smaller than expected. This does not match the natural distribution of the lesion level and seems to be random. In total, four patients (7%) dropped out of the interim analysis due to occurrence of exclusion criteria.

**Table 5 T5:** Administrative interim analysis of the completeness of laboratory data (flow cytometry) for each visit relative to the number of enrolled patients feasible for 'per protocol’ analysis

**Groups**		**Visit 1**	**Visit 2**	**Visit 3**	**Visit 4**	**Visit 5**
**Overall** n = 56	Complete data n	32	38	44	44	25
	(% of 'per protocol’ population)	(57)	(68)	(79)	(79)	(45)
**SCI T4 and above** n = 28	Complete data n	17	20	22	22	16
	(% of 'per protocol’ population)	(61)	(71)	(79)	(79)	(57)
**SCI T5 and below** n = 11	Complete data n	6	6	8	10	5
	(% of 'per protocol’ population)	(55)	(55)	(73)	(91)	(45)
**Control group** n = 17	Complete data n	9	12	14	12	4
	(% of 'per protocol’ population)	(53)	(71)	(82)	(71)	(24)

**Legend:** The completeness of the main laboratory data was calculated for the three groups relative to the number of enrolled patients feasible for 'per protocol’ analysis. The sample size calculation takes a 50% rate of drop out or missing values into account. Considering the drop out rate < 10% at the current stage of the trial, a 60% rate of data completeness is acceptable. Critical rates of overall completeness are observed at visit 1 and visit 5 and relate mainly to the control group and to patients with neurological level T5 or below.

### Statistical analysis

Data analysis of the primary endpoint consists of a comparison, between the 3 groups at the early and subsequent follow-up assessment points using one-way ANOVA or nonparametric tests, if appropriate. The analysis will be performed using the full dataset comprising all patients included according to the criteria as defined in the study protocol. In addition, in patients with complete intra-individual datasets also changes over time within the groups will be assessed with descriptive methods. Furthermore, in the case of a relevant amount of missing values, multiple imputation will be taken into consideration for verification of the analysis of the original data. Data obtained from patients treated with methylprednisolone will be primarily analyzed in a casuistic manner.

The statistical analysis of the administrative interim evaluation has been performed using SPSS for Macintosh, Version 19.0.

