### Sample size calculation

The primary endpoint is a difference in HLA-DR expression on monocytes exactly quantified by analysing antibody-binding molecules/cell within the first week (day 3–4) post-trauma. Numbers of patients to be enrolled were calculated on the basis of a pilot study (n = 26) [6]. The sample size calculation was performed for an effect size of 0.18. The type one error was be set to 0.05 (two-sided); type two error was set to 0.2. The number of patients eligible for evaluation (for testing the hypothesis by the one way anova) is 56 in total (software nquery, version 7.0). Due to an expected rate of drop-outs/missing data of 50% and non-parametric testing, where applicable, the number of patients to be recruited increases to 118 in total. The expected rate of drop-outs/missing data relates to the structural conditions of acute SCI care in terms of i) delayed transfer to specialized SCI trial centers after primary care in external non-specialized centers and ii) loss to follow up due to discharge from inpatient rehabilitation, particularly in the control group or in cases of mild incomplete SCI. Consequently, to allow for a completion of the study within a feasible time period consideration of missing values is unavoidable.

The sample size calculation was performed taking the asymmetric natural distribution of the neurological lesion level into account [20]. Injury to the cervical and high thoracic spinal cord has the highest incidence and represents the largest group of SCI patients. Thus, the relation of the 3 groups to each other was determined as follows based on the pilot trial data i) 41% (n = 48); ii) 26% (n = 31); iii) 33% (n = 39).

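### The article fixes the primary endpoint at one time window in the sample size section but tests it at several visits in the analysis section, so it is unclear which comparison carries the 5% error

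*Protocol article*

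**What the plan says.** **Sample size calculation.** The primary endpoint is a difference in HLA-DR expression on monocytes at one window, days 3 to 4 after trauma. The error rates are given once: "The type one error was be set to 0.05 (two-sided); type two error was set to 0.2". The size comes from one test: "The sample size calculation was performed for an effect size of 0.18", and "The number of patients eligible for evaluation (for testing the hypothesis by the one way anova) is 56 in total". The recruitment target then includes an allowance for a rank-based test: "Due to an expected rate of drop-outs/missing data of 50% and non-parametric testing, where applicable, the number of patients to be recruited increases to 118".

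**Statistical analysis.** The analysis of the primary endpoint is a comparison of the three groups "at the early and subsequent follow-up assessment points using one-way ANOVA or nonparametric tests, if appropriate". The same section limits within-group change over time to descriptive methods. It does not put that limit on the between-group comparisons at later visits.

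**Visit schedule (Abstract; Assessment time points).** There are five visits: before 31 hours, 31–55 hours, day 7, day 14 and 10 weeks. Extended windows are allowed for visits 2 to 5, but they are given in Figure 3, which is not shown in the text reviewed.

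**The concern.** The sample size section implies one confirmatory test. The analysis section puts several three-group tests under the heading of the primary endpoint. A reader of the final report could not tell from this article whether a significant difference at day 14 alone, say, would count as the primary result. If it would, the 0.05 used for sizing is not the error rate of the primary claim.

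Falling back on the sample size section does not fully settle this, because its window does not match a scheduled visit. The choice between ANOVA and a nonparametric test is also left open, with no criterion given. That is a smaller matter.

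**Working it through.** **1. The plan's own figure.** Inputs from the Sample size calculation section: three groups, alpha 0.05, power 0.80, effect size 0.18, 56 evaluable, 118 recruited.

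- One-way ANOVA power uses the noncentral F distribution with 2 and N − 3 degrees of freedom and noncentrality N × f².
- With f² = 0.18 (f = √0.18 = 0.424), N = 56 gives 79.5% power and N = 57 gives 80.3%. The stated 56 is reproduced to within one patient.
- Reading 0.18 as f itself would need 301, so f² is the reading that fits.
- Recruitment: 56 / (1 − 0.5) = 112. Dividing by 0.955, an assumed efficiency for a rank test, gives 117.3, close to 118.

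The stated size therefore belongs to **one** three-group test at 0.05, with no provision for several visits.

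**2. Does days 3 to 4 identify a visit?** Counted as elapsed days, it is 72–96 hours. If the first 24 hours are day 1, it is 48–96 hours. Visit 2 ends at 55 hours and visit 3 is nominally at 7 × 24 = 168 hours. The first count overlaps neither visit. The second overlaps visit 2 only from 48 to 55 hours. The extended windows might close the gap, but they cannot be read here.

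**3. Error rate if any visit may be claimed, each at 0.05.** For m independent tests the rate is 1 − 0.95^m:

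| Visits counted | 2 | 3 | 4 | 5 |
|---|---|---|---|---|
| Rate | 9.8% | 14.3% | 18.5% | 22.6% |

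Repeated measurements in the same patients are correlated, which lowers the rate. The article gives no correlation, so it is an assumption, varied here from 0 to 0.9. Three-group ANOVAs at five visits were simulated with no true difference, in two settings:

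- 56 complete patients (23/15/18, from "i) 41% (n = 48); ii) 26% (n = 31); iii) 33% (n = 39"), 20,000 runs;
- 118 patients (48/31/39) with the overall completeness in Table 5 (57, 68, 79, 79 and 45%), missing at random and independently by visit, 10,000 runs.

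Each cell gives the result for equal correlation between all visits, then for correlation that decays with visit distance.

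| Correlation | 56 complete | 118 with Table 5 completeness |
|---|---|---|
| 0 | 22.1 / 22.5% | 22.6 / 21.8% |
| 0.3 | 21.1 / 22.0% | 22.2 / 22.3% |
| 0.5 | 18.5 / 20.6% | 21.6 / 21.5% |
| 0.7 | 15.7 / 17.7% | 20.0 / 20.5% |
| 0.9 | 10.6 / 11.9% | 17.3 / 18.1% |

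The rates in the second setting stay higher because different patients contribute at different visits, so the tests are less alike. If missing visits cluster in the same patients, the rates move towards the first setting.

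**4. Test choice.** If both ANOVA and Kruskal–Wallis were run at one visit and the smaller p-value reported, simulation gives about 6.5–7%. Doing this at all five visits gives about 28%, 22% and 19% at correlation 0, 0.5 and 0.7.

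**5. After a fix.** One visit and one test at 0.05 give 5%, and the stated 56 stands. If all five visits stay primary under Bonferroni, each is tested at 0.05 / 5 = 0.01. The overall rate if independent is 1 − 0.99^5 = 4.9%. But 80% power at f² = 0.18 then needs 82 evaluable patients, and 56 give 57% power per visit.

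**The case against.** The strongest reply is that the sample size section already gives one window, one test and one alpha, and that the later comparisons are naturally read as supportive. On that reading, with the test fixed, the rate is 5%. The analysis section does not say that all five visits count, and nothing says that one significant visit is enough for a primary claim. The 23% end needs independence between repeated measurements in the same patients. Multiplicity rules and criteria for choosing a test are often left to a full protocol or SAP, which may exist. The stated aims are to characterise and explore, in an observational study.

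Most of this stands, and it limits the point. A reader might infer that the plan as written has a false-positive rate of 15–23%. The documents do not support that as a fact, because it rests on a claim rule and a correlation that they do not state. A reader might also infer that both tests will be run and the better one reported. The wording reads more naturally as a choice depending on assumptions, and the recruitment target already anticipates it.

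The reply does not remove the conflict. The article itself places the later group comparisons under the primary endpoint, and a SAP would still have to choose between the two statements. Nor does the window, taken against the nominal schedule, single out the visit that decides.

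**Conclusion.** The point holds as an internal contradiction with a conditional consequence. The two sections disagree on when the primary endpoint is tested, and the window in the first matches no nominal visit.

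- Only days 3 to 4 decide, test fixed: 5%.
- Any of the five visits may be claimed at 0.05: about 10–23% with complete data, or about 17–23% with Table 5 completeness, for assumed correlations from 0.9 to 0.
- Fewer visits counted: lower, for example at most about 18.5% for four.

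The open choice of test is minor: about 6.5–7% at one visit, and only if both tests are run and the better one reported. The conflict should be settled before the groups are compared, because it decides what counts as the primary result.

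**What to change.** Reconcile the two sections as follows.

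1. Name one scheduled visit, with its permitted window, as the sole confirmatory time point. State how it relates to days 3 to 4, given that visit 2 ends at 55 hours and visit 3 is at day 7.
2. Fix one test in advance at two-sided 0.05, for example ANOVA on log antibodies per cell, or Kruskal–Wallis, which the inflation to 118 already allows for.
3. Label the other visits secondary, or test them in a fixed sequence only after the primary comparison is significant.

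This changes wording only and keeps both the 5% and the 56 evaluable patients. At the overall completeness in Table 5, either neighbouring visit would supply more than 56: 118 × 0.68 = 80 at visit 2 and 118 × 0.79 = 93 at visit 3. These counts assume that the interim rates persist and that no further patients are excluded. The downside is that results at later visits can no longer be called primary.

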### Observation period

Observational time points (Figure 2) range from acute to sub-acute stages after SCI comparable to the pilot study [6]. Here, the time schedule corresponded to the hallmarks of parenchymal inflammation following SCI. The implementation of sub-acute assessments is in line with previous trials that demonstrated mid- and long-term alterations of the immune system after SCI [8,18,19].

The setting of defined time corridors instead of time points provides a more complete tracking of the participants. In order to prevent a high amount of missing datasets due to loss to follow-up, the protocol allows an inclusion at each documentation time point.

The administrative interim analysis of data completeness for the main laboratory parameters indicates - depending on the group or visit – a completeness of data between 24% and 91% with critical rates of completeness at visit 1 and visit 5, particularly in the control group (Table 5). As a consequence, the recruiting centers have been requested to enroll the patients as soon as possible after injury. Additionally, we intend to address the challenge of loss to follow up by travelling to external rehabilitation centers or by phone calls to remind patients of their study visit at the outpatient clinic. The rate of complete longitudinal datasets ranges between 18% and 36% but is expected to increase during the further trial course since trial routines are better established. Noteworthy, the sample size calculation takes 50% of missing values into account and was performed for one-way ANOVA. Repeated measure analysis requires lower sample sizes. Therefore, it seems feasible that a relevant amount of complete longitudinal datasets can be achieved also for the description of the intra-individual course of the SCI-IDS. Pursuing this study concept, serial investigations on short- and mid-term changes of the immunological function are provided.

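### Within-group change over time is described only in patients with complete datasets, which leaves about half or more of the interim samples out of the longitudinal description and probably selects more severe cases

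*Protocol article*

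**What the plan says.** The Statistical analysis section sets two rules. The comparison of the three groups, at the early and the later visits, uses the full dataset of all patients included under the protocol's criteria. In addition, "in patients with complete intra-individual datasets also changes over time within the groups will be assessed with descriptive methods". Multiple imputation is mentioned as something to consider, if much is missing, as a check on the analysis of the original data.

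The Discussion (Observation period) gives the interim position: "The rate of complete longitudinal datasets ranges between 18% and 36" (per cent), with an increase expected as trial routines settle. It recalls that the sample size allows for 50% missing values and was computed for a one-way ANOVA, and adds: "Repeated measure analysis requires lower sample sizes". From this it concludes that enough complete longitudinal datasets seem feasible.

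The Sample size calculation section names two sources of missing data. One is late transfer from non-specialised centres. The other is "loss to follow up due to discharge from inpatient rehabilitation, particularly in the control group or in cases of mild incomplete SCI".

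The section Possible consequences gives longitudinal characterisation of immunological markers as the objective. One secondary hypothesis in the Abstract concerns functional deficits that may outlast the acute phase.

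**The concern.** The rule for change over time is stated, not left open, and it bears on a named objective. It admits a patient only if every scheduled sample is present. The protocol tolerates inclusion at any time after the first 31 hours, so a late entrant cannot have a complete set, however well followed afterwards. Every sample from such a patient, and from anyone who misses one later visit, drops out of the longitudinal description.

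Two things are at stake. The first is precision: a small part of the collected data would carry the description of the course. The second is selection. Because the description is made within groups, a difference in completeness between groups would mainly cost numbers. Selection within a group distorts the course itself. If mildly injured patients are discharged early and lost, each SCI group's course is that of its longer-staying, probably more severe members, and severity is itself one of the study's hypotheses.

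The feasibility argument also needs a look, because it treats a smaller required sample size as if it answered the question of incomplete data.

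**Working it through.** **Inputs.** Table 5 (flow cytometry, 56 per-protocol patients), samples at visits 1 to 5:

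- T4 and above (n = 28): 17, 20, 22, 22, 16
- T5 and below (n = 11): 6, 6, 8, 10, 5
- Controls (n = 17): 9, 12, 14, 12, 4
- Overall: 32, 38, 44, 44, 25

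Complete datasets: 18% to 36% (Observation period). Complete is taken to mean all five visits, which the article does not spell out.

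**Samples collected.** 32 + 38 + 44 + 44 + 25 = 183 of 56 × 5 = 280 scheduled, or 65%.

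**Completers, if 18% to 36% is the range across groups.** The whole-number counts that round into this range and do not exceed any visit count are:

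- T4 and above: 5 to 10 of 28
- T5 and below: 2 to 4 of 11
- Controls: 3 or 4 of 17, since only 4 have visit 5

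Requiring the lowest group rate to be 18% and the highest 36% leaves totals from 12 (5 + 4 + 3) to 17 (10 + 4 + 3).

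- 12 completers: 12 × 5 = 60 samples used; unused 1 − 60/183 = 67%
- 17 completers: 17 × 5 = 85 samples used; unused 1 − 85/183 = 54%

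**Outer bounds, applying each rate to all 56.** 0.18 × 56 ≈ 10 and 0.36 × 56 ≈ 20 patients, so 50 or 100 samples used; unused 1 − 50/183 = 73% or 1 − 100/183 = 45%.

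**Selection.** Visit 5 samples exist for 16/28 (57%), 5/11 (45%) and 4/17 (24%). All SCI against controls is 21/39 against 4/17: odds ratio (21 × 13)/(18 × 4) = 3.8, Fisher p = 0.045. This fits the stated reason for loss as far as controls are concerned. The part about mild incomplete SCI cannot be checked, because no table gives completeness by AIS grade.

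**The sample-size sentence.** The plan's own figure comes first. The Sample size calculation section takes a two-sided 5% level and 80% power and arrives at 56 evaluable patients over three groups. On the effect it says only: "The sample size calculation was performed for an effect size of 0.18". The scale of 0.18 is not named. Taken as f² (variance of group means over error variance), with noncentrality N × 0.18 and 2 and N − 3 degrees of freedom, power at N = 56 is 79.5% and 80% is reached at N = 57. The stated 56 is therefore reproduced within rounding (f = 0.18 would give 301, and η² = 0.18 would give 48).

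For repeated measures the article gives no within-patient correlation ρ. Assuming equal correlation between visits and the same f² before adjustment, the error variance is multiplied by (1 + 4ρ)/5 for a mean over five visits and by 2(1 − ρ) for a change between two visits. N for 80% power, against 57 at a single visit:

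| ρ (assumed) | Mean of 5 visits | Change between 2 visits |
|---|---|---|
| 0.2 | 23 | 89 |
| 0.3 | 27 | 79 |
| 0.5 | 36 | 57 |
| 0.8 | 49 | 25 |

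The saving is real for a visit-averaged group effect at any ρ below 1. For change, it appears only when ρ exceeds 0.5.

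**Ten-week controls.** At the interim rate, 4/17 × 39 ≈ 9 of the 39 planned controls would have visit 5.

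**The case against.** The strongest reply is that the completer description is a supplement. The main group comparison uses every available sample at each visit, including 10 weeks, and multiple imputation is at least contemplated. That stands. A reader might infer that half the samples are lost to the trial; the documents do not support this, since the loss is confined to the description of change. Comparisons made visit by visit, however, do not estimate within-patient change, and imputation is offered only as a possible check.

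A reader might also infer that the repeated-measures sentence is wrong. It is not: it is unqualified, and it is true for some contrasts and correlations. What fails is the inference drawn from it.

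Nor does the complete-case rule cause the shortage of controls at 10 weeks. Those samples were not obtained, and no model restores them. It is equally tempting to say that the 50% allowance has failed at visit 5, but the allowance was set for an endpoint in the first week.

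Finally, the 18% to 36% is an interim rate. The protocol calls visits 1 and 5 critical and lists remedies: earlier enrolment, travel to rehabilitation centres and reminder calls. These may raise completeness. They do not alter a rule that drops a patient for one missed visit. The protocol does not link late transfer to severity, so the selection argument rests on discharge alone.

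**Conclusion.** The point holds for the description of change over time. At interim the rule would rest it on 12 to 17 of 56 patients, at most 4 of them controls, and leave about 54% to 67% of 183 collected samples unused for that purpose (45% to 73% at the outer bounds). The narrower range assumes that 18% to 36% is the spread across groups; both ranges assume that complete means all five visits, and both would shrink if completeness improves.

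That completers are a more severe subset is likely from the protocol's own account of discharge, but it is not shown by AIS grade. The step from a lower required sample size to the feasibility of complete datasets does not follow: needing fewer patients neither completes their data nor removes selection, and the planned description is not a powered analysis. The primary early comparison is unaffected.

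**What to change.** - Describe the course with a linear mixed model for repeated measures on all available samples from eligible patients: group, visit and group × visit, AIS grade as a covariate within SCI, and a covariance structure that the data can support. With so few controls at visit 5, a fully unstructured matrix may not be estimable.
- Report group-by-visit means and changes with confidence intervals.
- Keep the complete-case description as a sensitivity analysis, with numbers by group.
- Delete the sentence that repeated measures need lower sample sizes, or qualify it by contrast and assumed correlation.
- State that 10-week control estimates will be imprecise (about 9 of 39 at the interim rate) and that the model does not cure this.

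The cost is wording and routine programming, with no extra data. The downside is reliance on missing at random given group, AIS grade and observed values. This cannot be verified, but it is generally weaker than what the complete-case description needs.
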